#### Patient-reported outcome measures

Questionnaires will be given to patients in the clinic to take home and return by post in pre-paid envelopes. The Functional Assessment of Cancer Therapy-Hepatobiliary (FACT-Hep) total score will be used to measure disease-specific quality of life [39]. Fatigue will be measured with the Functional Assessment of Chronic Illness Therapy-Fatigue (FACIT-F) total score [40]. We will use the Activities-specific Balance Confidence scale (ABC scale) total score to assess fear of falls [41]. Anxiety and depression symptoms will be assessed via the Hospital Anxiety and Depression Scale (HADS) total subscale scores for anxiety and depression [42]. Self-reported physical activity will be assessed with the Godin Leisure-Time Exercise Questionnaire using the total leisure activity score [43].

#### Acceptability

We will distribute brief online surveys to patients within 1 h of their second exercise session in weeks 4 and 8 via Google forms. A link to the survey will be distributed via email, and patients will be asked to complete the survey as soon as possible. The survey involves nine Likert-like items on a 5-point scale ranging from 0 (*Strongly disagree*) to 5 (*Strongly agree*), as well as an open-ended section that allows patients to freely express their views. Survey items build on previous research [20] and relate to satisfaction with the technology and exercise sessions. The survey questions are available in the supplementary information files. The research team will meet monthly and decide whether the exercise protocol requires minor modification based on survey findings and feedback during the sessions.

Acceptability will also be assessed qualitatively with in-depth, semi-structured, one-to-one exit interviews with patients. A member of the research team experienced with telephone interviews ([name]), but not involved in intervention delivery, will contact all patients 1–4 weeks after completion of the final follow-up assessment. The interviews will be conducted remotely via telephone. The researcher will facilitate the interviews using a conversational-style approach whilst referring to a topic guide, which is informed by the capability-motivation-opportunity-behaviour (COM-B) model of behaviour [44] and by previous studies exploring experiences and perceptions of exercise [45, 46]. Topics will focus on patients’ perceived expectations, benefits, motives, and barriers to the intervention (see supplementary information for topic guide). The topic guide will be used flexibly to allow patients to raise additional issues which they consider important to the study. It is anticipated that each interview will last approximately 30–60 min.

Final assessments of acceptability will involve examining reasons for declining to participate amongst eligible patients, reasons for non-adherence to the exercise intervention, and reasons for dropout amongst discontinuing patients.

### Safety reporting

Reporting of adverse events will be conducted in line with NuTH’s policy on adverse event reporting for non-clinical trials of investigational medicinal products (CTIMPs). A member of the research team ([name]) will be responsible for determining the attribution and seriousness of adverse events and ensuring they are appropriately documented. All adverse events will be recorded in the Trial Master File. We will report serious adverse events that are deemed to be related to study participation to the trial sponsor and the relevant research ethics committee. Serious adverse events are defined as any untoward medical occurrence that results in death, is life-threatening, requires unplanned or prolonged hospitalisation, results in persistent or significant disability or incapacity, or results in a congenital abnormality/birth defect. Non-serious adverse events are defined as any untoward medical occurrence that do not fulfil any of the serious adverse event criteria [47]. Information on adverse events will be collected after written consent has been contained up until the 10-week follow-up. Patients enrolled into the study are covered by indemnity for negligent harm through NHS schemes. Newcastle University has insurance to cover for nonnegligent harm arising from the design of the research.

### Sample size

There are no clear guidelines on sample size requirements for non-randomised feasibility trials. Thus, our sample size is based on the minimum number of patients the research team considers sufficient to achieve the key aims of the feasibility study and the number that is achievable to recruit within a 6-month period [48]. Based on recruitment to ongoing studies at NuTH with similar participant eligibility criteria (e.g. ISRCTN16680540), we expect that at least three eligible patients per week will be identified. Assuming that 30% of eligible patients provide consent (which is a conservative estimate based on the mean recruitment rate in similar studies [49]), we will recruit at least 20 patients in a 6-month recruitment period. We consider this number of patients sufficient to provide sufficient information on feasibility and acceptability.

### Criteria for success

Based on a systematic review of recruitment, retention, and exercise adherences rates in patients with advanced cancer [49], this feasibility trial will be deemed successful if the following criteria are met:≥ 40% of eligible patients provide written consent to take part in the feasibility trial.≥ 70% of patients attend at least 14 out of 20 exercise sessions.≥ 75% of patients complete the FACT-Hep questionnaire at baseline and 10-week follow-up.No serious adverse events are attributable to the intervention or study procedures.

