**Methods:**

This is a protocol for a prospective, single-centre, single-arm, pretest-posttest feasibility trial. We aim to recruit 20 patients aged 60 years or older who have received treatment for HCC and are undergoing routine clinical monitoring. Patients will be invited to take part in two online, home-based, group exercise sessions per week for 10 consecutive weeks. The ‘virtual’ exercise sessions will be delivered in real time by an exercise professional through videoconferencing software. Each session will comprise 30 min of aerobic and resistance exercise performed at a moderate intensity, as guided by the 10-point Borg rating of perceived exertion scale. Feasibility outcomes include recruitment, retention, adherence, intervention fidelity, and safety. Acceptability of the intervention will be assessed using a mixed-methods approach via monthly online surveys and an exit telephone interview. Physical function, accelerometry-measured physical activity, mid-upper arm circumference, and patient-reported outcome measures (PROMS) will be assessed before and after the intervention to determine the feasibility of assessing outcome measures. Physical function outcomes include the short physical performance battery and Liver Frailty Index. PROMS include the Functional Assessment of Cancer Therapy-Hepatobiliary questionnaire, Functional Assessment of Chronic Illness Therapy-Fatigue questionnaire, Activities-specific Balance Confidence scale, Hospital Anxiety and Depression Scale, and the Godin Leisure-Time Exercise Questionnaire.

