#### Feasibility

Feasibility outcomes include recruitment rate, retention rate, intervention adherence, intervention fidelity, and safety. The definition and criteria for success for each feasibility outcome are presented in Table 1. Reasons for declining to participate in the study, and reasons for withdrawing from the study after providing consent, will also be recorded in a Consolidated Standards of Reporting Trials (CONSORT) flowchart.

**Table 1 Tab1:** Feasibility outcomes for this study

Outcome	Definition
Recruitment rate	The proportion of eligible patients who are approached and give informed consent to participate
Retention rate^a^	The proportion of patients who consent to take part in the study and complete the FACT-Hep questionnaire at both baseline and 10-week follow-up
Intervention adherence^b^	i) The mean proportion of exercise sessions attended by patients (assessed by attendance records kept by the intervention facilitator) ii) The mean proportion of exercise sessions completed at or above a moderate intensity, assessed via RPE (rating of ≥ 3 on the 10-point scale)
Intervention fidelity	Assessed by a research team member attending a 10% sample of the virtual exercise sessions using a standardised checklist to check whether the sessions are delivered in accordance with the protocol
Safety	The number and type (i.e. serious or non-serious) of adverse events that are related or possibly related to the intervention or study procedures

^a^The Functional Assessment of Cancer Therapy-Hepatobiliary (FACT-Hep) questionnaire was chosen for the assessment of retention rate because this is likely to be our primary outcome for a subsequent randomised controlled trial

^b^Adherence to the intervention will be evaluated only in patients who complete the study, defined as patients who complete the FACT-Hep questionnaire at both baseline and 10-week follow-up

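### The recruitment criterion uses only the consent proportion, so the success rule tests neither the assumed flow of three eligible patients per week nor the target of 20 patients in 6 months; this matters if flow falls to about half of plan or less

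*Protocol article*

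**What the plan says.** The Criteria for success section lists four conditions under which the feasibility trial is deemed successful. The one on recruitment reads "≥ 40% of eligible patients provide written consent to take part in the feasibility trial". The others concern attendance ("≥ 70% of patients attend at least 14 out of 20 exercise sessions"), completion of the FACT-Hep questionnaire by at least 75% of patients, and absence of attributable serious adverse events. Table 1, under Feasibility, defines recruitment rate as "The proportion of eligible patients who are approached and give informed consent to participate". Neither place mentions a number of patients recruited or a period.

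The number and the period stand in the Sample size section. It bases the size on "the minimum number of patients the research team considers sufficient to achieve the key aims of the feasibility study" and on what can be recruited in 6 months. It then gives two assumptions, "we expect that at least three eligible patients per week will be identified" and "Assuming that 30% of eligible patients provide consent", and concludes that "we will recruit at least 20 patients in a 6-month recruitment period". The abstract repeats the target as an aim: "We aim to recruit 20 patients aged 60 years or older".

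**The concern.** The target of 20 is the product of three things: eligible patients per week, weeks, and the proportion who consent. The success rule looks only at the last. The flow of eligible patients is taken from other studies at the same centre, and it is an assumption that a feasibility trial is well placed to check. No criterion and no outcome in Table 1 checks it.

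The article says that the results will inform the design of an adequately powered randomised trial. Whether that trial can recruit depends on flow multiplied by consent. A rule based on consent alone could return a favourable answer on recruitment when the centre has too few eligible patients. The attendance and retention criteria are proportions too, and the safety criterion has no minimum number of patients, so nothing else in the rule would register the shortfall.

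**Working it through.** **Inputs from the protocol article.** Flow of at least 3 eligible patients per week, 30% planning consent rate, 6 months and target 20 (Sample size); threshold 40% (Criteria for success). I take 6 months as 24 to 26 weeks.

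**The plan's own figure.** Recruited = flow × weeks × consent.
- 24 weeks: 3 × 24 = 72 eligible; 72 × 0.30 = 21.6.
- 26 weeks: 3 × 26 = 78 eligible; 78 × 0.30 = 23.4.

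Both agree with the stated minimum of 20.

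**What 40% implies at the planned flow.** 72 × 0.40 = 28.8 and 78 × 0.40 = 31.2. Meeting the proportion then means exceeding the target.

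**Where the proportion and the target part company.** At exactly 40%, 20 consents correspond to 20 / 0.40 = 50 eligible patients, which is 50/26 = 1.9 to 50/24 = 2.1 per week. Below that flow, 40% consent gives fewer than 20 patients. For example, 10 consents from 25 eligible patients is 40%, at a flow of 25/26 = 0.96 to 25/24 = 1.04 per week.

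**How likely this is.** My assumptions: the number eligible, n, is Poisson with mean 26 × flow; consents, k, are binomial(n, p); recruitment closes at 26 weeks. I summed over n and k to get P(k/n ≥ 0.40 and k < 20), that is, criterion met with fewer than 20 recruited.

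| Eligible per week | p = 0.40 | p = 0.45 | p = 0.50 |
|---|---|---|---|
| 3 (plan) | about 0 | about 0 | about 0 |
| 2 | 0.07 | 0.07 | 0.05 |
| 1.5 | 0.35 | 0.44 | 0.41 |
| 1 | 0.51 | 0.69 | 0.81 |

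If true consent is only the planning rate of 30%, the criterion is seldom met and the probabilities are lower: about 0 at 3 per week, 0.02 at 2, 0.08 at 1.5 and 0.15 at 1.

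**The reverse case.** On the plan's own assumptions (3 per week, 30% consent), the same model gives probability 0.79 of reaching 20 patients but only 0.03 of meeting the 40% criterion. With the number eligible fixed at 78, meeting 40% needs 32 consents (0.40 × 78 = 31.2), and P(k ≥ 32) is 0.025. Recruitment exactly as planned, about 23 of 78, is 29%: it meets the target and fails the criterion.

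**The case against.** The strongest case against is that nothing here is a contradiction. Table 1 defines a proportion, the criterion sets a threshold for that proportion, and the 20 is a sample size rather than a success threshold. Consent among eligible patients is a sensible measure of willingness to take part. The flow of three per week is given as a lower bound and rests on experience at the same centre with similar eligibility criteria. At that flow the gap vanishes, and at 2 per week it is small. The Study setting section says only that a 6-month recruitment period is anticipated. If slow flow simply lengthened recruitment, the shortfall in numbers might never arise. Finally, the CONSORT flowchart will show the counts whatever the verdict.

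Much of this stands. It limits the point to low flow with a fixed close, and it means that the proportion should be kept. It does not remove the point, because the plan itself calls 20 its minimum and derives it from a flow that the success rule never tests. Reporting a count in a flowchart does not alter a verdict that ignores it.

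A reader might infer that the trial is likely to be declared successful with about half its patients. The documents do not support that. Half the target needs a flow of about 1 per week, one third of plan, and nothing in the article suggests such a fall. It also needs recruitment to stop at 6 months and the other three criteria to be met, and the probabilities above do not cover those criteria.

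**Conclusion.** The point holds in a conditional form. The recruitment criterion and the Table 1 definition do not test the plan's assumed flow or its target of 20 in 6 months. At the planned flow there is no practical consequence. At half the planned flow (1.5 per week), with 40% to 50% consent, the chance of meeting the criterion with fewer than 20 patients is 0.35 to 0.44; at one third (1 per week) it is 0.51 to 0.81. These results rest on Poisson flow, binomial consent and closure at 26 weeks. The low flows and the consent rates of 40% to 50% are illustrative values, not figures from the documents.

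The percentage is a poor stand-in for the target in the other direction too, since the 30% planning rate lies below the 40% threshold. Any repair has to deal with both. The change is worth making because it can alter the verdict on recruitment and costs very little.

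**What to change.** 1. In Criteria for success, put the plan's own number beside the consent proportion: at least 20 patients consented within the 6-month recruitment period.
2. In Table 1, extend recruitment rate to report eligible patients identified per week, set against the assumed three, and patients consented per month.
3. Reconcile the 40% threshold with the 30% planning rate. Either bring the two figures into line, or state that 30% is a cautious planning figure and that recruiting at that rate is meant to fail the criterion. Without this step, adding the count would leave a trial that recruits exactly as planned meeting the number and failing the proportion.

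The cost is wording in three sections: Criteria for success, Table 1 and Sample size. The counts should be available from screening and the CONSORT flowchart; no further patients or assessments are needed. The downside is that a trial with slow patient flow could no longer be called successful on recruitment, even if most of those asked agreed to take part.

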### Data and statistical analysis

#### Quantitative analysis

The flow of patients throughout the trial will be reported in a CONSORT flowchart. Descriptive statistics will be used to present baseline characteristics, feasibility outcomes, and acceptability survey responses. Continuous variables will be described with the mean and standard deviation (SD), and categorical variables will be reported as frequency and proportion. Continuous data with an asymmetrical distribution will be summarised with the median and interquartile range. A paired *t*-test or Wilcoxon signed-rank test (depending on data distribution) will be used to evaluate changes in outcomes from baseline to post-intervention, with the mean difference and 95% confidence interval from the model presented. Data will be analysed per protocol (i.e. missing data at follow-up will not be imputed).

#### Qualitative analysis

Exit interviews will be audio-recorded and transcribed verbatim. Anonymised transcripts will be imported into NVivo qualitative data analysis software (version 12) and analysed using reflexive thematic analysis [50, 51]. This analytic method involves the researcher undertaking six iterative phases of familiarising themselves with the data, generating codes (where we will use an inductive approach), constructing themes, reviewing themes, defining and naming themes, and finally producing the report. All transcripts will be coded independently by one member of the research team, with a proportion (~50%) independently coded by a second team member. Throughout the process, the two researchers will work collaboratively to discuss and refine codes, as well as collating them to develop the potential themes and later reviewing to agree final themes and subthemes.

### Research ethics approval

An independent NHS Research Ethics Committee (Northeast — Newcastle and North Tyneside 2) has ethically approved the study (IRAS ID: 300809).

### Patient and public involvement

We have involved patients and other key stakeholders at various points during the intervention development process. We initially shared an outline of our proposal with the national patient support group: LIVErNORTH. Their members felt that patients with liver cancer would embrace the opportunity to take part in online exercise sessions with other like-minded individuals, particularly because of the COVID-19 pandemic, which has made many people feel even more isolated. They also felt that the exercise sessions may give patients a sense of control over their prognosis. Subsequently, we convened a multidisciplinary steering group that included patient representatives, healthcare professionals (e.g. physiotherapist and hepatologist), and clinical exercise physiologist. The steering group regularly met online to codesign the intervention based on the best available evidence, logistical concerns, safety, and ways to support intervention adherence. We also had in-depth telephone discussions with five patients currently living with HCC (two receiving supportive care and three receiving active treatment). They expressed their views on various aspects of the intervention, and wherever possible, their preferences were incorporated into the research design. Following the codesign process, we held an online focus group with people living with and beyond cancer to gather their feedback on the prototype intervention, which led to minor modifications to the protocol. Patients will continue to be involved in the study via monthly participant surveys as well as through a Patient Reference Group (PRG). The PRG will provide guidance on key issues such as recruitment and dissemination and feed directly into the steering group via the group chair.

### Modification of the protocol

Any modifications to the protocol will be agreed by the research team and trial sponsor and approved by an independent NHS Research Ethics Committee.

## Discussion

Patients with HCC typically face limited treatment options due to age-related morbidities and the advanced stage at which the disease is diagnosed. Most patients are not eligible for curative treatment and are offered palliative treatment or supportive care only [7]. As a consequence, maintaining QoL and day-to-day function through symptom management is critically important [10]. Strong evidence supports the efficacy of specific doses of supervised exercise training for addressing certain cancer-related symptoms, such as QoL, physical function, fatigue, and symptoms of anxiety and depression [11]. However, there are many barriers to implementing supervised exercise programmes within cancer care pathways, including economic pressures on healthcare systems and personal barriers for patients.

Telehealth exercise offers patients the opportunity to take part in virtually supervised group exercise in their own home [19]. This may remove some of the barriers for exercise participation and offers a relatively low-cost means of delivering exercise at scale for a patient population that covers a wide geographical location. Despite its potential, there are uncertainties relating to the feasibility, acceptability, and safety of telehealth exercise in people living with HCC.

This mixed-methods study will address uncertainties relating to the feasibility and acceptability of delivering live, online, home-based exercise to patients with HCC. The findings will inform whether any modifications are required to refine and optimise the intervention, and the assessment of outcomes will provide information on the likely size and variability of intervention effects. Collectively, the data generated will inform the design of a subsequent, adequately powered, randomised controlled trial to evaluate the efficacy of the telehealth exercise intervention.

## Data Availability

This manuscript does not contain any data. Supporting material is available as supplementary information files.
